# Study protocol for a cluster randomised controlled feasibility trial evaluating personalised care planning for older people with frailty: PROSPER V2 27/11/18

**DOI:** 10.1186/s40814-020-00598-x

**Published:** 2020-04-28

**Keywords:** Personalised care planning, Quality of life, Older people, Frailty, eFI, Cluster, RCT

## Abstract

**Background:**

Frailty is characterised by increased vulnerability to falls, disability, hospitalisation and care home admission. However, it is relatively reversible in the early stages. Older people living with frailty often have multiple health and social issues which are difficult to address but could benefit from proactive, person-centred care. Personalised care planning aims to improve outcomes through better self-management, care coordination and access to community resources.

**Methods:**

This feasibility cluster randomised controlled trial aims to recruit 400 participants from 11 general practice clusters across Bradford and Leeds in the north of England. Eligible patients will be aged over 65 with an electronic frailty index score of 0.21 (identified via their electronic health record), living in their own homes, without severe cognitive impairment and not in receipt of end of life care. After screening for eligible patients, a restricted 1:1 cluster-level randomisation will be used to allocate practices to the PROSPER intervention, which will be delivered over 12 weeks by a personal independence co-ordinator worker, or usual care. Following initial consent, participants will complete a baseline questionnaire in their own home including measures of health-related quality of life, activities of daily living, depression and health and social care resource use. Follow-up will be at six and 12 months. Feasibility outcomes relate to progression criteria based around recruitment, intervention delivery, retention and follow-up. An embedded process evaluation will contribute to iterative intervention optimisation and logic model development by examining staff training, intervention implementation and contextual factors influencing delivery and uptake of the intervention.

**Discussion:**

Whilst personalised care planning can improve outcomes in long-term conditions, implementation in routine settings is poor. We will evaluate the feasibility of conducting a cluster randomised controlled trial of personalised care planning in a community population based on frailty status. Key objectives will be to test fidelity of trial design, gather data to refine sample size calculation for the planned definitive trial, optimise data collection processes and optimise the intervention including training and delivery.

**Trial registration:**

ISRCTN12363970 – 08/11/18.

## Background and rationale

Frailty is a condition characterised by reduced biological reserves and increased vulnerability to adverse outcomes [1]. Frailty has characteristics of considerable clinical importance, including higher reversibility at early stages than disability and higher predictive value than chronic disease for adverse outcomes [2]. Single disease management frameworks and targets are less relevant for older people living with frailty, who frequently have multi-morbidities, personal predicaments and social problems [3]. Current best practice suggests that care for older people with frailty should be proactive and person-centred, responsive to personal experiences of illness, individual priorities and predicaments [1, 4, 5].

Personalised care planning (PCP) is a promising way to achieve this shift towards proactive, person-centred care in frailty [4–6]. It is an anticipatory, negotiated series of guided conversations between a patient and a suitably trained individual to clarify goals, options and preferences and develop an agreed plan of action [4]. The process aims to ensure that individual values and concerns shape how care is provided, instead of a focus on individual disease management. In PCP, shared decision-making is a crucial mechanism, involving a collaborative discussion of management goals (goal setting) and developing an agreed plan for achieving these goals (action planning). Shared decision-making enables linkage to additional mechanisms for improving outcomes through more effective self-management, better care coordination and better access to community resources (social support) [4].

A 2015 Cochrane review summarised evidence from 16 international randomised controlled trials (RCTs) and identified that PCP for long-term conditions (LCTs) can improve physical and mental health and self-management capability. Effects appear greater when PCP is more comprehensive and integrated into routine care [4]. However, the majority of studies focused on single LTCs; no studies were identified that selected participants on the basis of frailty. Furthermore, a comprehensive evaluation of PCP in the UK has identified widespread, poor implementation [7, 8].

In the UK, the NHS long-term plan sets out the blueprint and key ambitions for the health service over the next 10 years [9]. The plan includes a focus on establishing primary care-based multidisciplinary teams to provide tailored support for older people living with frailty to enable them to live independently at home for longer. It is therefore essential that promising interventions, such as PCP, are designed to be sufficiently robust and flexible to facilitate integration with commissioning and provider organisations, prior to rigorous definitive trial evaluation. Age UK, the largest voluntary sector organisation representing older people in the UK, developed an integrated personalised care planning (IPCP) service in partnership with older people, their families and carers. Although the service was piloted, further research is required to optimise the service and evaluate its effectiveness. We have collaborated with the Age UK National programme to optimise the IPCP service and accurately identify those who are most likely to benefit from the PCP based on their level of frailty and health and social care use. The result is the Personalised Care Planning for Older People (PROSPER) intervention, designed to improve quality of life for older people with frailty and reduce use of health and social care services.

Here, we describe the protocol for the feasibility trial evaluation of PROSPER compared with usual care (UC) to inform the design of a definitive RCT.

### Aim and objectives

The overall aim of this trial will be to assess the feasibility of conducting, and to inform the design of, a definitive RCT to investigate the clinical and cost-effectiveness of PROSPER compared with UC.

Specific objectives will be to determine:
Appropriate methods to identify, approach and select general practices to participate in the trial.Appropriate methods to screen and consent potential participants to the trial, and the extent to which blinding can be maintained.Recruitment and follow-up rates of general practices and participants.How the sample size should be refined for the definitive trial.How data collection processes can be optimised.If the intervention can be further optimised, including through strategies to monitor and enhance reliability and validity of the intervention (fidelity of intervention training, delivery, receipt and enactment).If proposed outcome measures are feasible and acceptable to participants.

## Methods

### Trial design

PROSPER is a multi-centre, two-arm, feasibility cluster RCT. A cluster is defined as a general practice or a group of practices where the practices share significant staff and/or services, or were due to merge during the trial period. The cluster design was appropriate because the intervention was envisaged to be a multidisciplinary team-based intervention, delivered at the level of the general practice. An intervention embedded within primary care would also mean there would have been a high risk of contamination in an individually randomised trial from practice staff treating UC participants.

We also plan to embed a mixed-methods evaluation, informed by the MRC guidance for process evaluation of complex interventions [10] and the NIH Behaviour Change Consortium framework [11].

### Study setting

Participants will be recruited from 11 clusters in Bradford and Leeds, West Yorkshire. These locations cover a range of multi-ethnic rural and urban populations, so ensuring the generalisability of findings. Four of the 11 clusters will be sampled for the process evaluation.

### General practice (cluster) eligibility

General practices in Bradford and Leeds who use SystmOne, EMISWeb, Vision or Microtest primary care electronic health record systems will be eligible for inclusion. Practices with an existing or planned PCP service for older people with frailty that has significant overlap with the PROSPER model will not be eligible.

### Participant eligibility

Following agreements from the general practices to participate, all patients at a practice will be screened for eligibility by a practice administrative staff. The eligibility list will be further reviewed by a lead GP to avoid inappropriate contact being made.

Patients meeting *all* of the following criteria at time of screening will be eligible for inclusion:
Aged 65 or over.Frailty defined by the electronic frailty index (eFI) [12] score ≥ 0.21.Willing and able to give informed consent (or provide a personal consultee).

Patients meeting *any* of the following criteria will not be eligible for inclusion:
Resident of a care home at time of screening.Registration on the Gold Standards Framework (GSF) or end of life care.Coded diagnosis of severe dementia or a Montreal Cognitive Assessment (MoCA) score of ≤ 10 at baseline.Deemed inappropriate by their general practitioner (GP) (documented reason).Member of the household currently or previously participated in the trial.

### Carer involvement

Where the participant or their consultee has consented to the carer’s involvement, they will also be included. Carers lacking the capacity to provide written informed consent will not be included.

### General practice recruitment and randomisation

A range of approaches will be used to engage with general practices including local National Institute for Health Research Clinical Research Networks (NIHR CRNs), professional networks and practices listed on the Public Health England (PHE) website [13].

Practices will be randomised on a 1:1 basis either to implement the intervention or continue with usual care (UC) only, using an algorithm for covariate-constrained randomisation to achieve balanced allocation between the trial arms on sample size and baseline characteristics expected to be potential confounding factors [14]. Randomisation will be performed by the statistical team at the Clinical Trials Research Unit (CTRU). Following randomisation, the CTRU will inform the practice manager of the allocation to allow trial procedures to be implemented. Knowledge of the allocation will be restricted to staff in the practice multidisciplinary team (MDT) who will be involved in the delivery of the intervention. MDTs may include a variety of staff from GPs to community matrons. We will seek to maintain blinding of practice staff not directly involved in intervention delivery. Instances of un-blinding will be recorded.

### Participant recruitment/randomisation

To allow for scheduling of the intervention delivery and ensure that a similar number of participants are recruited from each general practice, eligible participants will be invited to consent to data collection in a phased approach. Following cluster randomisation, the CTRU will periodically generate a random sample of eligible participants to approach. Eligibility lists from each cluster will be ranked according to eFI to ensure a similar distribution of eFI scores that are randomly sampled across the clusters and between trial arms. For participants randomly sampled, eligibility will be re-confirmed by a practice staff prior to sending letters of invitation for trial participation (data collection). This process will be the same in both trial arms. PROSPER recruitment uses an opt-out approach, i.e. where an individual pro-actively declines to be contacted by a researcher by returning a negative expression of interest, to maximise potential for participant recruitment. This will allow researchers’ access to patient contact details after the opt-out period has ended and is aligned with previous research in this area [15, 16].

If there is no response to the invitation within 14 days, a researcher blinded to allocation will contact the potential participant by phone to discuss the study. If an individual is interested, the researcher will make an appointment to visit them. If not, the reason will be recorded, if possible. Once a participant is registered in the study, the Age UK delivery team will receive notification of those in the intervention arm and proceed to make contact. Participants in the control arm will continue to receive usual care.

The process for assignment of interventions is outlined in Fig. 1.

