### Trial consent or assent

Participant consent, recruitment and collection of baseline data will be undertaken in the potential participant’s own home by a researcher blind to cluster allocation. Home visits will be made to reduce participant burden and facilitate the assessment of capacity and cognition. Before consent researchers will make an assessment of the patient’s capacity to consent, using the Mental Capacity Act (MCA) framework (2005) [17]. Individuals lacking capacity to consent will not be excluded from this study as they may still benefit from engagement with the intervention. If a potential participant lacks capacity to consent, they will be asked to nominate a personal consultee to advise on their behalf. If the potential participant is unable to identify a personal consultee, the GP will be requested to identify an appropriate potential personal consultee. If a personal consultee is not available, no further contact will be made.

Following participant consent or consultee assent, researchers will administer the Montreal Cognitive Assessment (MoCA). Individuals scoring less than 10 will be deemed ineligible because they would be unable to take part in the shared decision making aspects of PCP. A carer will be identified (if available) and after consent; in the intervention arm, the practice administrative staff /PIC worker will be notified which patients have been registered.

Reasons for declining involvement will be noted if provided. The right of a patient (and carer) to refuse participation without giving reasons will be respected.

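### Practice staff re-check eligibility after cluster randomisation, wave by wave, with no requirement that the re-checker be blind, and one registration notice could reveal the arm to administrative staff

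*Protocol article*

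**What the plan says.** The steps are spread over four sections of the protocol article.

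- **Participant eligibility.** At the outset, "all patients at a practice will be screened for eligibility by a practice administrative staff". Then: "The eligibility list will be further reviewed by a lead GP to avoid inappropriate contact being made". A GP may exclude a patient as inappropriate, with a documented reason. The abstract places randomisation after this screening.
- **General practice recruitment and randomisation.** After randomisation, "the CTRU will inform the practice manager of the allocation". The next sentence sets the limit: "Knowledge of the allocation will be restricted to staff in the practice multidisciplinary team (MDT", further narrowed to those members who will deliver the intervention. The team may include GPs. The article aims to keep other practice staff blind and will log un-blinding.
- **Participant recruitment/randomisation.** Invitation is staged: "eligible participants will be invited to consent to data collection in a phased approach". The sample is drawn centrally: "Following cluster randomisation, the CTRU will periodically generate a random sample of eligible participants to approach". Then comes the practice step: "For participants randomly sampled, eligibility will be re-confirmed by a practice staff prior to sending letters of invitation for trial participation". The process is stated to be identical in both arms. A blinded researcher telephones only after the letter has gone out. Once a participant is registered, the Age UK delivery team is told who is in the intervention arm.
- **Trial consent or assent.** Here the recipient of the notice is different: "in the intervention arm, the practice administrative staff /PIC worker will be notified which patients have been registered".

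**The concern.** In a cluster trial that recruits individuals after randomisation, the main threat is that someone who knows the arm influences who enters. The plan guards against this with random sampling by the trials unit and with researchers blind to allocation. The re-check sits between those two safeguards. It acts on patients already sampled and is finished before the blinded researcher makes contact, so a removal made there cannot be corrected later.

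If the re-checker knows the arm, removals could differ between arms, for instance because delivery capacity matters in one arm only. That would affect the make-up of the invited group and the recruitment rates by arm. Recruitment rates, methods of screening and consent, and the extent to which blinding holds are all stated objectives, and recruitment is one of the areas for the progression criteria. A weakness left here could also carry over into the definitive trial. The 12-month between-arm intervals are a secondary matter, since no formal testing is planned.

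**Working it through.** No figure in the article bears directly on this point, so the check is mainly a comparison of sections.

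**1. Timing.** Sampling follows cluster randomisation and is repeated. Each sample is re-checked before its letters are sent. Registrations from an early wave can therefore occur, and be notified, before a later wave is re-checked.

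**2. Who re-checks.** The article specifies only a member of practice staff. Role and blinding are both left open.

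**3. Who may know the arm.**

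| Section | Who learns the allocation or of intervention-arm registrations |
|---|---|
| General practice recruitment and randomisation | Practice manager; delivering members of the multidisciplinary team, which may include GPs |
| Participant recruitment/randomisation | Age UK delivery team |
| Trial consent or assent | Practice administrative staff and/or the personal independence co-ordinator (PIC), intervention arm only |

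The third row does not fit the restriction in the first and names a different recipient from the second. A notice sent in one arm only identifies that arm to whoever receives it. Administrative staff are also the group that screens, so they are plausible candidates for the re-check. Separately, The PROSPER intervention section places the delivery workers inside the practice, which could reveal the arm once delivery to early waves has begun.

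**4. Whether the safeguards cover the re-check.** Screening before randomisation protects the initial list, but the re-check reopens it afterwards. Identical steps in both arms do not blind the person carrying them out. Blinding of non-delivery staff is an aim, and the notice works against it. Logging un-blinding records a breach without preventing it.

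**5. Illustration of size.** Inputs from the Sample size section: 400 participants, 200 per arm, 33% consent. Assumed, with no basis in the article: an extra 10% of sampled patients removed in one arm, their mean outcome 0.5 SD below that of all sampled patients.

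- Invitations needed: 400 / 0.33 = 1,212, or 200 / 0.33 = 606 per arm.
- Extra removals in that arm: 0.10 × 606 = 61.
- Would-be participants among them: 61 × 0.33 = 20. Because sampling is periodic they can be replaced, so composition may change without the number recruited falling.
- Shift in that arm's mean: 0.10 × 0.5 / (1 − 0.10) = 0.056 SD.

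A second model removes the worst fraction f on a normally distributed trait that has correlation r with the outcome. The shift is r × φ(z_f) / (1 − f), where φ is the standard normal density and z_f the f-quantile:

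| f (assumed) | r = 0.3 | r = 0.5 | r = 1.0 |
|---|---|---|---|
| 5% | 0.033 | 0.054 | 0.109 |
| 10% | 0.058 | 0.097 | 0.195 |
| 20% | 0.105 | 0.175 | 0.350 |

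The answer depends entirely on the assumed inputs.

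**The case against.** The strongest reply is that the article never says the re-checker knows the arm. It aims to keep non-delivery staff blind, records breaches, and makes the extent of blinding an objective, so the trial is partly designed to measure this weakness. The slash in the consent section may mean either recipient, and the figure showing the assignment process is not visible. Practice staff cannot put anyone forward; they can only remove someone the trials unit has sampled. Screening, eligibility and reasons for non-participation are already to be summarised in line with CONSORT. The article may leave the re-checker's role to the full protocol.

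Much of this stands, and it rules out three stronger readings that a reader might infer:

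- *That invitations are filtered by people who know the arm.* The text leaves this possible but does not state it. Nothing says that the person notified and the person re-checking are the same.
- *That re-checking staff apply the inappropriate-for-contact judgement afresh after randomisation.* That judgement belongs to the GP, with a documented reason, and the criteria apply at screening. With the abstract's sequence, the GP review appears to precede randomisation already, so there is no call to move it.
- *That the protection is undone.* Central sampling from lists ranked by frailty score, and blinded contact, consent and baseline assessment, all remain in place.

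The reply does not dispose of the notice. That is a conflict between steps the article itself sets out, not detail left to another document. Followed as written, it can tell the staff group that screens which arm the practice is in before later waves are re-checked.

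**Conclusion.** The point holds as an open route to identification bias, not as a demonstrated bias. It rests on three things in the text: the re-check falls after randomisation and recurs, nothing requires the re-checker to be blind, and the sections disagree on who is told of intervention-arm registrations. It also needs one inference, that administrative staff, or others who have learned the arm, may do the re-check. The stated safeguards reduce the risk without closing it.

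The size cannot be estimated from the article. The figure of about 0.06 SD, and the wider range in the second table, only show what given assumptions would imply. The main exposure is to recruitment rates by arm and to the lessons carried into the definitive trial.

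**What to change.** 1. Reconcile the three sections on who learns the allocation. Send intervention-arm registration notices to the delivery team only, or send identical notices to administrative staff in both arms.
2. State that the re-check is done by a staff member who has not been told the allocation and is outside the delivery team; the practice manager, who is told, would not qualify.
3. Limit the re-check to objective changes since screening, such as death, leaving the practice, care home residence, end of life registration or a severe dementia code. Any other removal should need a documented reason from a clinician who is blind to allocation. This also limits the harm if the arm becomes apparent from the delivery workers' presence.
4. Within the CONSORT-style summary already planned, report removals at re-check by arm and wave.

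The cost is wording, one named role and one redirected notice. The small downside is that very small practices may find it awkward to keep one staff member unaware of allocation.
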